### Additional analyses

Descriptive statistics showing the measurements over time will be presented whenever appropriate. Serious adverse events and cases of dropouts will be analyzed descriptively.

Interrater reliability will be assessed by independent raters for SCID diagnoses and LIFE ratings as well as for the treatment adherence. As a measure of consistency between measures of the same class, intraclass correlations (ICCs) will be calculated based on independent ratings of three raters each. In order to assess the internal consistency of the treatment adherence scales, Cronbach’s *α* will be measured. Further, treatment adherence will be assessed by comparing the mean scores for each treatment group on the SECT and EFST subscales by calculating *t* tests.

### Quality assurance, blinding, monitoring, and methods against bias

Clinical report forms (CRF) and standard operations procedure [12] have been developed and are available to all sites before starting the research protocol. These forms are updated on a regular basis as per the evolving needs of the study. Education of local study managers and training of diagnostic clinicians (raters) and therapists of both interventions were conducted during the first months at several central workshops. Further central workshops are conducted regularly to train new diagnostic clinicians and therapists and for the purpose of recalibration and monitoring in order to prevent rater and therapist drift. Each rater and therapist first has to successfully complete a certification process before becoming an active study assistant. For the diagnostic clinicians, a certification process is implemented, whereby, firstly, a gold standard is rated; secondly, the diagnostic assessment of a dummy patient is videotaped; and thirdly, one of the first study patients is videotaped. Ratings are approved by two experienced clinicians at the lead study center. Similarly, for therapists, the certification process includes videotaping a dummy group therapy session (30 min) for each condition, which has to be approved by two experienced therapists at the lead study center.

Across the course of the study, raters and therapists are controlled for reliability and adherence by supervising trainers. In regular intervals (once per month), conference calls for raters and therapists each are conducted for supervision to minimize the differences between the centers. For adherence assessment, two time slots (90 min each) of each therapy session will be videotaped. Of each treatment group, three sessions per therapist will be randomly selected and evaluated to measure the adherence to treatment protocol by independent clinicians blind to the diagnosis and treatment condition. To control for reliability, about 30% of SCID and LIFE interviews will also be taped and evaluated by a second clinician.

To ensure the performance according to the study protocol and the quality of the study, monitors visit each site and evaluate using the SOP and CRF at several points (1 during the initiating phase, and at least 1 during accrual time). The monitors check the completeness and plausibility of the data and align the study data to the original data (source data verification). This is accomplished by accessing the original subjects’ charts. The subjects give their permission for this procedure within the informed consent form. The monitor writes a protocol focusing on deviation from the SOP. Each study center is bound to correct any deviation from the SOP as soon as possible.

### Safety aspects

The clinical course of bipolar disorders implies relapses of high risk across the duration of the research. All study contributors assure to observe participant psychopathology carefully at each point of contact. Patients are enrolled in the study during a euthymic phase of the bipolar disorder; however, it is to be expected that depressive and/or manic episodes may occur during the course of the study and the occurrence of the same does not imply study discontinuation. As long as individuals are capable of participating in the group format, they are welcome to participate in the group therapy days. In critical health situations, the group therapist may offer an individual therapy session to provide additional practical and therapeutic support. All additional psychotherapeutic contact with the participants has to be noted down on the study protocol. If required, participants will be supported in liaising with and securing inpatient medical care.

The study follows a strict procedural protocol, and professional observations and communications with patients about their health issues during the study participation are a basis of correct clinical decisions. All contributors are familiar with the protocol and communicate about serious adverse events (SAEs) with the local principal investigator immediately irrespective of whether the event is causally related to the study. SAEs are defined as all fatal or life-threatening events (e.g., suicidal attempt), events that cause hospitalization or longer duration of hospitalization, or events that cause grave disabilities. The local study site is required to document and report SAEs immediately to the central study site. A report is kept in the study file of the participant.

The study has an internal safety board, independent study-related monitors, and an international advisory board (DSMC) as a steering committee. The day-to-day adherence to the study protocol is monitored by the respective principal investigator at each participating institution, who engages in a fortnightly telephone conference where procedural and logistical matters are discussed under the supervision of the head center and principal investigator (PI). In addition, the head center monitors the adherence to the protocol, data assessment, and processing by visiting study centers upon their initiation and yearly throughout the course of the study. At these visits, permission to proceed and requirements to implement necessary changes are discussed both verbally and with written feedback (i.e., via email). The PI then monitors the implementation of necessary changes to meet the protocol requirements. A Data Monitoring Committee (DMC) will be installed consisting of an independent statistician and two supporting clinical psychologists.

### Ethical issues and considerations

In regard to the protection of patients’ data, all patient files are stored in locked cabinets and rooms in line with the university or clinic’s local policies and legal requirements. A code is assigned to each study patient, which is used to file assessment and treatment information in the central server and data management system. Data management and analyses are entirely confidential and under no circumstances includes the name or personally identifying information of an individual patient.

A number of ethical considerations are relevant to the current study. It is notable that the study comprises a group therapy comparison with a targeted intervention (SECT) comparable to an active control group (EFST). Ethically, this is preferable to a classical controlled study, i.e., where patients are assigned to a waiting list, no treatment, or offered treatment as usual. Similar to in SECT, EFST participants receive an information booklet at the start of the intervention and while EFST therapists do not offer the tailored intervention topics such as in SECT, EFST therapists utilize all general therapeutic skills at their disposal and as per their therapy training, e.g., focusing on patients’ emotional experiences, reinforcing positive coping and strengths. Further, EFST therapists do not withhold illness-related information when requested by the patient. Psychoeducation is considered a key component in both therapy conditions.

This study hypothesizes that SECT may be a preferential intervention to EFST. SECT is tailored for bipolar patients based on the existing empirical evidence and clinical factors. However, it should be noted that the intervention in its current form—while considered safe—as of yet lacks empirical support. The monthly workshop format of the intervention is also novel. In other patient groups receiving individual therapy, less frequent sessions appear to impact outcomes negatively (e.g., PTSD and depressed patients, see [34, 35]). However, this may not be the case for patients in remission as has been shown in some studies (e.g., [36]). Indeed, the monthly format is proposed to increase opting-in, particularly for patients living in more rural areas who may have long distances to travel in order to engage in therapy. While therapy is only offered once a month, it should be noted that the “dosage” of therapy is relatively high, with an 8-h day being equivalent to 42-h sessions a week within a month. However, it is ethically notable that participants may not engage in individual psychotherapy external to the study in the 6 months prior to or during the course of the intervention. In instances where patients wish to commence individual psychotherapy during their study participation, patients are free to exercise their right to drop out and are considered to be lost to attrition. Despite this, it cannot be ruled out that patients’ knowledge of these exclusion criteria does not inform their own choice to forgo individual psychotherapy during their participation in the trial.

It is important to acknowledge that as with all RCTs, the current study involved the randomization of patients to either an active or (relatively) passive therapy condition. It is inevitable that clinicians may have an intuition or preference as to which condition may serve the patient’s interests at a given stage in the course of their illness. To eliminate the possibility of such preferential treatment against the interests of the study and research ethics, randomization is blindly completed by the lead study center (who only receives the patient’s age, gender, and number of past episodes to inform the normal distribution of the treatment groups).

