### Primary and secondary outcome measures

To examine the effect of the psychotherapy groups, the trial entails one primary outcome measure (relapse) and several secondary outcome measures: time to relapse (LIFE), relapse rate (LIFE), days missed at work/school (record, interview), and social functioning level [32].

Relapse is defined as the development of a new affective (either depression, [hypo] mania, or mixed) episode that meets the diagnostic criteria or results in a hospital admission. Relapse will be assessed every 6 months using the structured LIFE interview (at t2 [end of treatment], t3 [6 months after t2], and t4 [12 months after t2]). The LIFE leads to reliable information regarding the progression and course of illness, time in remission, development of new affective episodes (relapse), and also other mental disorders (co-morbidity). For example, patients are asked at t2, t3, and t4, “The last time we spoke you reported … [description of affective state at the time, e.g., ‘very depressed with problems sleeping’] … How has it been since then? … Since when have you been feeling better/worse?” This is followed with a formal rating based on DSM criteria (“Psychiatric Status Rating”) making note of when the change occurred (“Change Points”) leading to the collection of weekly ratings for the episode. Patients are encouraged to be specific regarding the changes. The interviewer facilitates this by asking questions such as “Was that in November?” and “Did that happen before or after the holiday season?”

Measurements of symptomatology (QIDS-C/SR, YMRS, ASRM), social functioning, and quality of life are assessed to integrate the patient’s everyday perspective (FAST).

Assessment of these outcomes as indicated by changes in these measures over time allows us to address our main hypotheses, i.e., whether SECT versus EFST shows reduced relapse rates, less missed days from work/school, less days spent in the hospital, lower health costs, improved treatment compliance, higher social functioning, and improved neurobiological functioning.

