### Statistical analysis

The question as to whether specific psychotherapy can prolong the time until relapse will be addressed by non-parametric survival analyses involving log-rank or Wilcoxon statistics and sensitivity analyses for the ITT (intent-to-treat) sample and the PP (per-protocol, required is participating in at least 75% of treatment sessions) sample. The time-dependent evolution of group-specific hazard rates will be investigated by parametric models addressing the differences in the dynamics of relapse in both intervention arms. Cox regressions will be performed to identify the risk factors for the probability of relapse and time until relapse if the proportional hazard assumption will not be negated. Our planned analyses will allow to identify if the types of participants with missing outcomes look different to those observed outcomes and whether this pattern might be different by arm: treatment arm with no missing primary outcome at primary time point, treatment arm with missing primary outcome at primary time point, control arm with no missing primary outcome at primary time point, and control arm with missing primary outcome at primary time point. Secondary endpoints like symptomatology, days missed at work/school, or social functioning level will be described on a univariate level and enter multivariable group comparisons on the base of an ANCOVA (with the factor kind of intervention (2) and time points (2 to 4) using baseline as a covariate) and involve stepwise variable selection. Based on the results for these covariates, methods such as principal component analysis or latent variable modeling will finally be considered to identify the risk factors for the probability of relapse and time until relapse. We have the intention to use the CONSORT statement for reporting the outcome and final results of this randomized controlled trial.

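### Patients who wish to start individual psychotherapy are filed as lost to attrition; keep those who still consent in LIFE follow-up and count their relapses in the ITT analysis

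*Protocol article*

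**What the plan says.** Under Ethical issues and considerations, the restriction itself is limited in time: "participants may not engage in individual psychotherapy external to the study in the 6 months prior to or during the course of the intervention". The next sentence has a wider trigger, "In instances where patients wish to commence individual psychotherapy during their study participation", and its consequence is that "patients are free to exercise their right to drop out and are considered to be lost to attrition". Participation runs to month 18, whereas the intervention lasts up to 5 months (Design and procedure).

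Three other statements bear on this:

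- Primary and secondary outcome measures: "Relapse will be assessed every 6 months using the structured LIFE interview", that is at t2, t3 and t4, with changes dated retrospectively.
- Statistical analysis: time to relapse is addressed by "non-parametric survival analyses involving log-rank or Wilcoxon statistics and sensitivity analyses for the ITT (intent-to-treat) sample" and for the per-protocol sample. The section also plans to "identify if the types of participants with missing outcomes look different to those observed outcomes and whether this pattern might be different by arm".
- Safety aspects: affective episodes are expected during the study, and "the occurrence of the same does not imply study discontinuation".

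The article gives no explicit censoring rule and does not say that follow-up continues for patients who take up individual therapy.

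**The concern.** Starting another therapy is a change of treatment after randomisation. An ITT analysis would normally keep following such a patient and count later relapses. Here the change is recorded as loss to follow-up, so the primary outcome is missing from then on.

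Log-rank and Cox methods assume that censored patients have the same relapse risk as comparable patients who stay under observation. That is doubtful here for two reasons. The wish for individual therapy may be connected with how the patient is doing. It may also differ between a structured skills programme and an unstructured support group.

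The scope adds to the problem. A patient who starts therapy in, say, month 10 is outside the period that the restriction covers, yet is still filed as attrition before the primary time point at month 18.

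The handling is also uneven. A patient who has an affective episode stays in the study. Under Safety aspects, so does one who receives an extra individual session from the group therapist in a crisis. One who seeks individual therapy elsewhere leaves.

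**Working it through.** **Does the rule lead to censoring?** The article does not say so, but its parts point that way. The patients count as attrition, no continued interview is described, and the monthly relapse rate in Sample size calculation is given for patients at risk, without dropouts. In a log-rank analysis, a patient lost without a recorded relapse is censored at the last assessment.

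**Inputs from Sample size calculation.** Relapse 4% per month in the control arm (taken as a hazard of 0.04); HR 0.50 as the relevant effect and 0.46 for N=300; dropout 12% over 18 months; α = 0.05.

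**Assumptions.** Exponential times, 150 per arm, two-sided test (the article does not state sidedness), 18 months of follow-up. q is the fraction of impending relapses that go unrecorded because the patient left first to start therapy. The document gives no value for q.

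**The plan's own figure.** Schoenfeld events for HR 0.50: 4 × (1.96 + 0.84)² / (ln 0.5)² = 65.3, so 66. With the stated inputs this needs a total N of about 169-185, depending on how dropout and the monthly rate are read, not 360. The stated sizes come out (360, 297, 196) only if 0.12 is used as a monthly dropout hazard. That is a separate matter, but it explains why baseline power below is well above 80%.

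**Formulas.**
- Background dropout hazard g = −ln(0.88)/18 = 0.0071 per month.
- Probability of a recorded relapse in an arm with hazard λ: P = λ(1−q)/(λ+g) × (1 − e^(−18(λ+g))).
- Events D = 150 × (P_EFST + P_SECT).
- Observed HR = true HR × (1 − q_SECT)/(1 − q_EFST).
- Power = Φ(√(D/4) × |ln observed HR| − 1.96).

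**No therapy-related loss.** HR 0.50: P = 0.4855 and 0.2849, D = 115.6, √(115.6/4) × 0.693 = 3.73, power 96%. HR 0.46: D = 112.7, power 98%.

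**Equal loss, q = 20% in both arms, HR 0.50.** Observed HR 0.50; D = 92.4; power about 91%. Events and some power are lost, but the HR is not biased.

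**Unequal loss, q = 10% SECT and 25% EFST.**
- HR 0.50: observed 0.50 × 0.90/0.75 = 0.60; P = 0.3641 and 0.2564, D = 93.1; √(93.1/4) × 0.511 = 2.46; power 69%.
- HR 0.46: observed 0.46 × 0.90/0.75 = 0.55; D = 90.5; power about 80%.

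**Loss the other way, q = 25% SECT and 10% EFST, HR 0.50.** Observed 0.50 × 0.75/0.90 = 0.42, which flatters SECT.

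**Smaller loss, 8% background, q = 5% SECT and 10% EFST.** Recorded loss is then about 8% and 11%. HR 0.50 appears as 0.53 and power is about 91%. At HR 0.46 power is about 95%.

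**No true effect (two-sided rejection rate).**
- Equal q: 5-6%.
- 5-point difference (15% vs 10%): observed HR 0.94 (0.85/0.90), about 6%.
- 10 points: 9-10%.
- 15 points (25% vs 10%): observed HR 0.83 (0.75/0.90), D = 120.2, about 17%.
- 20 points: 23-26%.

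Log-rank simulations at N=300 with the same q values gave the same power and type I error for the 15-point scenarios. A second simulation, with 6% background loss and censoring 0-3 months before relapse, supplied the 10-point and 20-point rates. It moved a true HR of 0.50 to between 0.45 and 0.63, depending on which arm lost more.

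**The case against.** The wording gives patients a right to leave, in an ethics section, and does not order their removal. An article condenses a longer protocol, and censoring rules are often left to that document or to the SAP. This stands in part: censoring is implied, not stated. But the article does state the attrition rule, and an analysis plan cannot supply interviews that were not held.

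A reader might infer that the rule removes just those patients who are deteriorating. The documents do not support that. No reason for seeking therapy is given. Patients enter in remission, and a well patient may want individual therapy once the group has ended. Those in crisis have a route within the study through an extra session with the group therapist. A link with prognosis is plausible, not established.

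A reader might also infer that the ITT analysis is broken. That goes too far. An ITT analysis is planned, relapses dated up to the last LIFE interview still count, episodes do not end participation, and missing and observed patients are to be compared by arm. That comparison can reveal a pattern but cannot recover the lost relapses.

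Finally, the 10% and 25% fractions are large. On top of 12% background dropout they imply about 21% recorded loss in EFST, against the 12% planned. This objection stands, which is why the smaller scenario is shown as well.

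**Conclusion.** The point holds in a limited form. As written, the rule turns a treatment change into loss of the primary outcome, over a longer period than the restriction behind it. Whether this biases the result depends on whether the loss differs by arm, and the document settles neither the size nor the direction. Equal loss costs some power only. With the assumed 10% and 25%, power at N=300 falls from about 96% to 69% at HR 0.50, and from about 98% to 80% at HR 0.46, which is still the nominal design power. With a 5-point difference the damage is small in either direction.

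A more alarming figure can be produced: at a true HR of 0.59 the same fractions leave about 40% power. But 0.59 is not a value in the protocol, so that figure should not carry the argument.

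This is a cheap improvement that should be made. Confidence is moderate, because the fractions are assumptions and the full protocol may say more about follow-up.

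**What to change.** Separate starting individual psychotherapy from withdrawal of consent:

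- Record the date and type of any individual psychotherapy begun during the study.
- Continue the scheduled LIFE interviews at t2-t4 for every patient who still consents, and count their relapses in the ITT analysis.
- Reserve attrition for withdrawn consent or lost contact. The right to leave is unaffected.
- Add a sensitivity analysis that censors at the start of individual psychotherapy.
- Reconcile the two periods under Ethical issues and considerations (course of the intervention, and whole study participation). This does not require changing the therapy restriction itself.

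The cost is a change of wording, a short record of therapy start, and interviews that are already in the schedule. The drawback is that the ITT contrast then includes the effect of outside therapy and may be slightly diluted. The sensitivity analysis gives a view of the result without it.

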### Randomization

Central randomization either to SECT or to EFST will control for random allocation to both interventions at each research site. For this purpose, an independent statistician developed randomization lists using a centrally computer-generated block-designed randomization procedure stratified by center. Only the principal investigator and his proxy have direct access to the randomization lists. Randomization results are directed at the local study manager.

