### Blinding

Throughout the whole study, clinician raters are kept blinded. Results of the individual randomization process will be given only to the local study managers and the group therapists by the principal investigator. Study teams will be trained on how to avoid unblinding during the diagnostic process and team meetings. The statistician who will later analyze the results is as well kept blinded throughout the whole study.

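### Two sections describe allocation differently, and the principal investigator can both read the lists and release the results, so concealment is not assured

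*Protocol article*

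**What the plan says.** The protocol article describes allocation in three places.

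- **Randomization.** The sequence was made by a third party: "an independent statistician developed randomization lists". The method is a "centrally computer-generated block-designed randomization procedure stratified by center". No stratum other than centre is named. On access: "Only the principal investigator and his proxy have direct access to the randomization lists".
- **Blinding.** "Results of the individual randomization process will be given only to the local study managers and the group therapists by the principal investigator".
- **Ethical issues and considerations.** The authors accept that clinicians may prefer one arm for a given patient, and they offer the allocation procedure as the protection against this: "randomization is blindly completed by the lead study center". The same sentence says that the only patient data the lead centre receives are "age, gender, and number of past episodes to inform the normal distribution of the treatment groups".

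The section on design and procedure gives the order of events: screening, consent and confirmed eligibility come first, then individual randomization.

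**The concern.** There are two linked problems.

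First, the description is inconsistent. A list stratified by centre alone has no use for age, gender or number of past episodes, yet the ethics section gives these items a purpose in shaping the arms. The reader cannot tell which procedure was used, so cannot judge whether the analysis matches it.

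Second, there is custody. The independent statistician makes the sequence, but the trial lead can read it and issues the results. Patient characteristics reach the lead centre as part of the same process. Concealment is meant to ensure that nobody who can influence whether, when or in what order a patient is allocated knows the next assignment. As written, the plan does not ensure this.

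At stake is the comparability of the arms on the primary relapse comparison. The planned log-rank or Wilcoxon test, as described, includes no adjustment for the three characteristics, so it would not correct an imbalance produced at allocation.

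**Working it through.** The plan gives no figure to reproduce, and no arithmetic applies. The check is a comparison of the three statements.

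**1. Can both descriptions of the method be complete?** Under "block-designed randomization procedure stratified by center", the next assignment depends on two things only: the centre and the next unused position on that centre's list. Age, gender and past episodes do not enter. There are then four ways to read the ethics section:

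- The three items are recorded only to monitor balance. This fits the Randomization section, but the ethics section does not say so; it says that they inform the distribution of the groups.
- They are formal allocation factors, as further strata or in a balancing rule. The Randomization section, which names centre alone, is then incomplete.
- They are used at someone's discretion. This would contradict both the prepared list and the statement that randomization is done blindly.
- They are sent but not used. The stated purpose is then wrong.

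Under each reading at least one of the two sections needs correcting. The article does not say which reading applies. (The phrase about a normal distribution presumably means balance between the arms.)

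**2. Who can know the next assignment?** The Randomization section gives the principal investigator and proxy direct access to the lists. Anyone who can read the list knows the next assignment with certainty, whatever the block size. Not stating the block size therefore gives no protection here.

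**3. Who releases it?** According to the Blinding section, the results go to "the local study managers and the group therapists by the principal investigator". Steps 2 and 3 together put knowledge of the sequence and its release in the same hands.

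**4. Does the word blindly resolve this?** Only if the person who completes randomization at the lead centre cannot see the list. The two people named as having access are the principal investigator and proxy, and the principal investigator issues the results. Blindly may mean blind to the patient's identity or to the clinician's preference. It cannot mean blind to the sequence for anyone who holds the list.

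**5. What could list access allow?** A departure from the list is one possibility. Another leaves the list intact: if two patients at one centre are waiting, the order in which they are processed decides who receives which arm. This matters when the fix is designed, because comparing assignments with the list alone would not reveal a change of order.

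**The case against.** The strongest reply is that the ethics sentence is meant as a safeguard. It says that allocation is done blindly, that the lead centre receives only three items, and that the purpose is to keep clinicians' preferences out. Generation is central and independent, access is limited to two people, and recruiting clinicians, the usual route to selection bias, are given none. Allocation already follows consent and confirmed eligibility. The wording about the distribution of the groups may be loose English for monitoring balance, and a condensed article may leave further strata or balancing rules to the full protocol.

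Much of this stands. The protective intent is clear, and the harmless reading is possible. But a fuller document cannot make two conflicting published statements agree as they are worded. A protective intent also does not alter the stated custody rule, which leaves the sequence readable by the person who releases it.

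A reader might go further and infer that concealment failed, or that prognosis was used to steer patients. The document supports neither: no section says that anyone departed from the list or chose an arm. A reader might also treat past episodes as a strong relapse predictor and compute a bias in the hazard ratio. The Background says only that younger patients with few episodes showed better effects of psychotherapy. That concerns response to treatment, not baseline relapse risk, and any computed bias would rest on invented inputs. Finally, it is implied, not stated, that the principal investigator belongs to the lead centre, which is itself one of the recruiting hospitals. The custody point does not depend on it.

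**Conclusion.** The point holds as an inconsistency plus an avoidable custody risk. The Randomization section and the ethics section do not describe the same allocation mechanism. Read together, the Randomization and Blinding sections let the person who releases allocations know the next one. Concealment is not assured; it has not been shown to fail.

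The size of any bias cannot be estimated from the document, and it may be zero. The conclusion assumes only that the three sections mean what they say about strata, list access and release of results. If the three characteristics turn out to be recorded for monitoring only, the inconsistency is settled by a sentence, but the custody point remains.

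**What to change.** For patients still to be randomized:

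- Have the independent statistician, or another party independent of recruitment and treatment, hold the lists and release one allocation at a time, only after the patient is registered. The custodian should not be the analysing statistician, whom the Blinding section keeps blinded.
- Remove the principal investigator's and proxy's access to future allocations.

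Make the Randomization section and the ethics section describe one mechanism:

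- If it is blocks within centre, state that age, gender and number of past episodes play no part in assignment, and stop sending them before allocation.
- If they were in fact formal factors, name the method and account for the factors in the analysis.

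For patients already randomized, have the independent statistician compare the allocations with the lists as generated, in order of registration, and report any deviation.

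Do not introduce minimisation now. Recruitment began in August 2015, and a change of method would split the trial between two allocation schemes.

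The cost is a small administrative change in who releases allocations, a correction to the wording, and one audit of existing records. Sample size, assessments and treatment are unaffected.
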